**Methods:**

This two-arm, parallel, cluster-RCT with a 6-month intervention and 6-month follow-up period foresees to randomize a total of 20 communities/villages from 4 townships in a 1:1 ratio to either intervention or control. Within these communities, a total of at least 256 community residents will be enrolled. The experimental group will receive a multi-level intervention based on the socioecological model supplemented with a multi-dimensional empowerment approach. The control group will receive information only. The primary outcome is the reduction of modifiable unhealthy lifestyles at six months, including smoking, excess alcohol consumption, physical inactivity, unbalanced diet, and overweight/obesity. A reduction by one unhealthy behavior measured with the Healthy Lifestyle Index Score (HLIS) will be considered favorable. Secondary outcomes include reduction of specific unhealthy lifestyles at 3 months, 9 months, and 12 months, and mental health outcomes such as depression measured with PHQ-9, social outcomes such as social support measured with the modified Multidimensional Scale of Perceived Social Support, clinical outcomes such as obesity, and biomedical outcomes such as the development of gut microbiota. Data will be analyzed with mixed effects generalized linear models with family and link function determined by outcome distribution and accounting for clustering of participants in communities.

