##### Exclusion criteria

Less than 5 residents of the community in question meet the participant eligibility criteria.

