### Randomization and allocation concealment

In this cluster-RCT, recruitment and baseline data collection will be conducted prior to randomization. Cluster randomization, which is necessary for implementation of community-level interventions, mitigates concerns of within-community/village contamination, and improves the feasibility of on-site intervention, will be performed at the community/village level. A total of 20 eligible communities/villages will be randomized using a computer-based random number generator (www.random.org) and assigned to either the intervention group or the control group, with 10 communities/villages in each group. A covariate adaptive procedure will be used to minimize the *P* value from a joint *F* test (1000 iterations) to facilitate covariate balance [34, 35]. Several location level covariates will be considered, including number of village residents, and mean age and sex ratio of residents.

Allocation concealment will be ensured through central randomization [36]. Specifically, an independent statistician will generate a block randomization sequence with randomly permutated block size (4–8) and 1:1 allocation ratio. A sequential list with resulting random numbers will be provided to the study center that recruits villages. Only after participation of a village is confirmed, will the study center reveal labels of the random sequence to the trial team delivering interventions.

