### Sample size

The primary outcome is the improvement of modifiable unhealthy lifestyles, with a reduction by at least one unhealthy lifestyle at 6 months considered a favorable outcome (coded 1) and any other outcome unfavorable (coded 0). According to a previous study, the prevalence of at least one unhealthy lifestyle in Chinese community residents is 89.6% [2, 37]. According to an analysis of the previous two survey waves of the CMEC, it is expected that 2 percent of the control group participants will achieve a favorable outcome. We assume that a 10% percent increase of participants with favorable outcome in the intervention group (to 12% in total) constitutes a minimally important difference.

To achieve a power *of* 0.80 to obtain a statistically significant signal at α <  = 0.05 for p_1_ = 0.02 vs. p_2_ = 0.12 with a chi-squared test of independence, the sample size is estimated as 204 (102 per group). To account for participant attrition of estimated 20%, recruitment target is 128 participants per group, with a total sample of 256 participants for assessment and evaluation.

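### The 0.80 power behind 204 (256 recruited) assumes independent participants in a trial that randomises 20 villages, so it holds only if the village ICC is essentially zero

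*Protocol article*

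**What the plan says.** The section Randomization and allocation concealment says that randomisation "will be performed at the community/village level", "with 10 communities/villages in each group". The abstract promises models "accounting for clustering of participants in communities", and the Data analysis section specifies random intercepts for subject nested in village plus a fixed effect for town.

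The Sample size section is built differently. Its aims are "To achieve a power *of* 0.80" and "to obtain a statistically significant signal at α < = 0.05". From an analysis of the two earlier CMEC waves "it is expected that 2 percent of the control group participants will achieve a favorable outcome", and 12% in the intervention group is taken as the smallest important result. The number is then obtained "with a chi-squared test of independence, the sample size is estimated as 204 (102 per group"). The only later adjustment is 20% attrition, giving 128 per group and 256 in total; the abstract words this as a minimum. No ICC, design effect, cluster size or number of villages enters the calculation.

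One further passage bears on village size. A site is excluded if "Less than 5 residents of the community in question meet the participant eligibility criteria".

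**The concern.** A chi-squared test of independence treats each participant as a separate piece of information. Participants from one village share a group manager, a local clinician, a WeChat group and monthly activities (Table 1; Tools for intervention implementation). Their outcomes may therefore be correlated, and any positive correlation shrinks the effective sample. The sizing model thus disagrees with both the unit of randomisation and the planned analysis.

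What is at stake is the power claim for the primary outcome. If 0.80 is printed beside the final result, it describes an individually randomised trial of the same size, not this one.

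**Working it through.** **Inputs from the article.** Control 0.02, intervention 0.12, alpha 0.05, power 0.80, 1:1 allocation, 10 villages per arm, 20% attrition. Sidedness is not stated; two-sided reproduces the article's figure.

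**Inputs assumed, because the article gives none.** ICC 0.01, 0.02 and 0.05; CV of village size 0 and 0.6.

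**1. Reproduce the stated figures.** The pooled proportion is 0.07.
- Null variance term: 2 × 0.07 × 0.93 = 0.1302, square root 0.3608.
- Alternative variance term: 0.02 × 0.98 + 0.12 × 0.88 = 0.1252, square root 0.3538.
- n per arm = [(1.960 × 0.3608 + 0.8416 × 0.3538) / 0.10]² = 101.005, rounded up to 102, or 204 in total. Power at 102 per arm is 80.4%.
- Attrition: 102 / 0.8 = 127.5, rounded up to 128, or 256 in total.

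Both figures match exactly with a design effect of 1, so they contain no hidden allowance for clustering.

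**2. Add clustering.** Evaluable participants per village: m = 102 / 10 = 10.2. Design effect DE = 1 + ((1 + CV²)m − 1) × ICC. Effective n per arm = 102 / DE. Power is the normal probability below (0.10 × √(effective n) − 1.960 × 0.3608) / 0.3538.

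| Assumed ICC | DE, CV 0 | Effective n per arm | Power, CV 0 | DE, CV 0.6 | Power, CV 0.6 |
|---|---|---|---|---|---|
| 0.01 | 1.09 | 93.4 | 77% | 1.13 | 75% |
| 0.02 | 1.18 | 86.1 | 73% | 1.26 | 71% |
| 0.05 | 1.46 | 69.9 | 64% | 1.64 | 59% |

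For very small ICCs the loss is slight: with equal villages, power is 79.7% at ICC 0.002 and 78.6% at 0.005.

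**3. Check by another route.** Beta-binomial outcomes were simulated in 10 villages per arm with 10 or 11 evaluable participants each, and compared by a cluster-level t-test on 18 degrees of freedom. Power was 79.6% at ICC 0, and 76.3%, 73.6% and 65.3% at ICC 0.01, 0.02 and 0.05. These agree with the equal-size column.

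**4. Recruits needed for 80%, for context only.** With 20 villages fixed, solving n = n₀ × (1 + (n/10 − 1) × ICC) gives n = n₀(1 − ICC) / (1 − n₀ × ICC / 10) per arm. The lower figures below use n₀ = 101.005 and the upper ones n₀ = 102. Doubling and dividing by 0.8 gives 278–281, 310–314 and 485–494 recruits at the three ICCs. If village size is instead held at 10.2 evaluable and villages are added, the totals are about 276, 300 and 370, but that means roughly 22, 24 and 29 villages instead of 20.

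**The case against.** **The mixed model already handles clustering.** It does so for the inference. It does not restore power lost to correlation.

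**A fuller protocol may hold an ICC.** The article shows its whole derivation, and the result equals the unclustered answer. A positive ICC elsewhere could not be reconciled with 204 and 256.

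**The target is a minimum, and it includes a margin.** More than 256 may be enrolled, but the 0.80 is attached to 256. The 20% margin is committed to expected dropout. If nobody dropped out (12.8 per village, equal sizes), power would be 84.7%, 81.0% and 70.4% at the three ICCs, so even then it falls short at 0.05.

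**The ICC is unknown and may be small.** This stands. At a control rate of 2%, an ICC of 0.05 implies a between-village standard deviation of √(0.05 × 0.02 × 0.98) = 3.1 percentage points around a mean of 2, which is a strained value for that arm. The fixed effect for town and the covariate-balanced allocation may also reduce residual between-village variation, by an amount the article does not quantify.

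**Stronger readings that the article does not support.**
- A reader might infer that the power is known to be as low as 64%. That figure is conditional on an assumed ICC.
- A reader might deduct a few more points for using a t reference with 18 degrees of freedom. The simulation in step 3 already uses that reference and lands on the same figures, so the deduction would count the loss twice.
- A reader might take the site exclusion rule as proof that village sizes will differ widely. It sets a minimum number of eligible residents, not an enrolled cluster size. Sizes may vary, but no CV is given.
- A reader might expect a null result to be misread as evidence of no effect. The article does not say how a null result would be interpreted.

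**Conclusion.** The point holds. The arithmetic is right for an individually randomised trial; the error is applying it to a village-randomised one. The stated 0.80 rests on an unstated design effect of exactly 1 and is met only if the ICC is essentially zero.

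The shortfall depends on assumed inputs. With equal villages it is about 3, 7 and 16 percentage points below 80% at ICC 0.01, 0.02 and 0.05. With a CV of 0.6 it is about 5, 9 and 21 points.

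**What to change.** 1. Estimate the village-level ICC of the favourable outcome from the two CMEC waves that already supply the 2% control rate. Say that this reflects untreated change and may miss correlation created by village-level delivery, which bears mainly on the intervention arm. For that reason show a range, not one value.
2. In the Sample size section, state DE = 1 + ((1 + CV²)m − 1) × ICC with m about 10, and give the CV used and its source.
3. Replace 0.80 by the resulting power. Possible wording: *With 256 recruited and 204 evaluable participants in 20 villages (about 10 per village), power to detect 2% versus 12% at two-sided 0.05 is X% to Y% for ICCs from A to B and a cluster-size CV of C.*

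Cost: one re-analysis of existing cohort data and one rewritten paragraph. The stated power becomes less favourable. Correcting the statement needs no extra recruitment; whether to add participants or villages is a separate decision for the sponsor.

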### Intervention

#### Intervention model and theory

The 3SLIFE intervention is primarily based on the framework of the socioecological model and comprises interventions at the individual, family and community levels [38]. Smart device-based and offline interventions will be implemented at each level. Drawing on multi-dimensional empowerment theory, we aim to promote self-management ability among participants at the individual, family and community levels by strengthening self-management skills, fostering social engagement, and personalization of goals [29], rather than relying exclusively on external instruction [39]. Details of the framework are provided in Fig. 2.

**Fig. 2 Fig2:**
[figure not shown]
3SLIFE framework outlining the intervention details

#### Intervention design and strategy

The intervention group will receive intervention for the first 6 months after recruitment into the study. In the second 6 months, instructed intervention will be terminated, but self-management of lifestyles can continue based upon participants’ decision and quarterly assessment will continue to observe participants’ maintenance of healthy lifestyles.

According to the 3SLIFE, interventions will take place at three levels: (1) individual level (microsystem): providing medical consultation services and health knowledge, one-to-one health coaching, and requiring participants’ voluntarily documentation of their daily lifestyles; (2) family level (mesosystem): communicating with family members about participants’ lifestyle status, making healthy lifestyle improvement plans with family members, and improving participants’ self-management ability through family supervision; (3) community level (macrosystem): organizing online and offline community activities, creating healthy environments, and improving self-management ability of healthy lifestyles through online healthy lifestyle documentation and offline community activities.

The control group will receive placebo interventions unrelated to healthy lifestyles and chronic disease risk factors (e.g., information about the hospital visit process) for the first 6 months after enrollment. Participants in control group will also complete quarterly assessment. In the second six months, the placebo interventions will be terminated while quarterly assessments continue. To ensure that the control group can benefit from the same healthy lifestyle interventions, all participants in the control group will have access to the same program as the intervention group at the end of the trial followed up with assessments as previously given provision of consent.

More details of intervention strategies are listed [32], in Table 1 and Fig. 2 according to the TIDieR framework [32].

**Table 1 Tab1:** Intervention strategies for control and intervention groups

	Control group	Intervention group
**Individual**		
Intervention	**·**Content: Providing medical consultation services and knowledge unrelated to healthy lifestyles (e.g., hospital treatment procedures) **·**Material: Homemade videos or weblinks to videos, and pictures **·**Provider: Group manager **·**Where: WeChat group **·**Schedule: For 6 months. Providing topics unrelated to healthy lifestyles twice a week	**Knowledge:** **·**Content: Providing medical consultation services and regular daily health knowledge related to healthy lifestyles and other topics (e.g., hospital treatment procedure) **·**Target: Changing misconceptions about healthy lifestyles; increasing knowledge about healthy lifestyles **·**Material: Homemade videos or weblinks to videos, and pictures **·**Provider: Group manager **·**Where: WeChat group **·**Schedule: For 6 months, providing topics related to healthy lifestyle once a day, and providing topics unrelated to healthy lifestyles twice a week **Skill:** **·**Content: One-on-one health coaching **·**Target: Guiding changes in unhealthy lifestyle; guiding engagement in healthy lifestyles; providing skills in maintaining healthy lifestyles **·**Materials: Live streaming platform, online course (e.g., exercise, diet), recipe (guided by the Mediterranean diet), tools (e.g., fitness aids such as elastic bands, medication aids) **·**Provider: Health professor, group manager **·**Where: WeChat and Tiktok live streaming platform, and homemade videos **·**Schedule: Being scheduled for 6 months. Live classes are offered twice a week; daily recipe and daily exercise guidance were provided
Self-management	None	**Empowerment:** **·**Content: Participants’ voluntarily online documentation of their daily lifestyle **·**Target: Self-management of health lifestyles with encouragement, self-supervision, and supervision from others **·**Materials: Gift (household goods) **·**Where: WeChat and offline activities **·**Provider: Group manager **·**Schedule: Inviting all participants document daily lifestyles (scheduled for 12 months) One-to-one online communication once a week to remind unhealthy lifestyle modification or healthy lifestyle maintenance (within 6 months). Being awarded with gifts consisting of daily necessities (e.g., soap and laundry detergent) for participants who document lifestyles well for that month in monthly offline activity (within 6 months)
**Family**		
Intervention	**·**Content: For highly vulnerable participants (e.g., living with two or more chronic diseases), communicating with family members about participants’ health need unrelated to healthy lifestyle (e.g., healthcare reimbursement) **·**Provider: Group manager and local medical workers **·**Where: WeChat, phone **·**Schedule: For 6 months. Online communication with family members if needed	**Communication:** **·**Content: For highly vulnerable participants (e.g., living with two or more chronic diseases) or those requesting this, inviting family members to learn about participants’ lifestyle status and health needs unrelated to healthy lifestyle **·**Target: Learning about participants’ lifestyles **·**Where: WeChat, phone, and face-to-face communication **·**Provider: Group manager and local medical workers **·**Schedule: For 6 months. Inviting family members to attend monthly offline activities and talking about participants’ health status one to one; online communicating with family members once a month about the participant's lifestyles in the previous month
Self-management	None	**Empowerment** **·**Content: For highly vulnerable participants, development and revision of lifestyles modification plan (e.g., exercise three times a week and documentation); co-supervision **·**Target: Promoting family members’ participation in managing participants’ lifestyles; increasing participants' confidence in maintaining healthy lifestyles **·**Where: WeChat, phone, and face-to-face communication **·**Provider: Group manager and family members **·**Schedule: Making healthy lifestyles plan (e.g., exercise three times a week) in the first month post-intervention; online communicating with family members once a month about the participant's lifestyles (within 6 months). Asking family member to join and help with documentation of daily lifestyles (within 6 months)
**Community**		
Intervention	**·**Content: Holding community health activities unrelated to healthy lifestyles (e.g., infectious disease prevention); providing free medical consultations **·**Provider: Group manager and local medical workers **·**Where: Local medical centers **·**Schedule: For 6 months. Providing offline community activities once a month and offline free medical consultations each quarter.	**Mutual support** **·**Content: Holding online activities (e.g., healthy lifestyle knowledge quizzes) and offline activities related to healthy lifestyle and other topics **·**Target: Increasing interpersonal interaction among participants in the same groups; improving participants’ knowledge and skills of healthy lifestyles **·**Where: WeChat group, local medical centers **·**Materials: Health tools (e.g., fitness aids such as elastic bands, medication aids) **·**Provider: Group manager and local medical workers **·**Schedule: Being scheduled for 6 months. Providing online community activities once a week (healthy lifestyle knowledge quizzes), and providing offline community activities once a month **Environments** **·**Content: Creating a healthy environment **·**Target: Creating environment/atmosphere to motivate participants’ healthy lifestyles **·**Where: WeChat group, local medical centers **·**Materials: Health tools (e.g., fitness aids such as elastic bands, medication aids) **·**Provider: Group manager and local medical workers **·**Schedule: Providing tools and announcing the rules for documentation, rules for awarding prizes as soon as the intervention is underway
Self-management	None	**Empowerment** **·**Content: Medical consultation and peers’ encouragement **·**Target: Developing healthy lifestyle with the help of medical staff and peers who perform well in healthy lifestyles **·**Where: WeChat group, local medical centers **·**Provider: Group manager, doctors (from geriatric department, cardiovascular department, nutrition department, rehabilitation department of top three hospitals), local medical workers, and socially active peers **·**Schedule: Holding offline free medical consultations each quarter, giving advice on healthy lifestyles for participants. Sending gifts to participants who do well in online activities (once a month) and who have improved health status (once a quarter). Encouraging peers who perform well in healthy lifestyles to share their experiences of healthy lifestyle maintenance and encouraging other participants in offline activities, once a month

#### Tools for intervention implementation

Intervention and control groups in each community will be assigned one trained group manager and one local medical doctor or nurse with at least 5 years professional experience. The 3SLIFE intervention will be implemented through online and offline activities. Online interventions will be delivered through WeChat and Tiktok Channels, two mainstream live streaming apps in China, to guide diet, exercise, and medication, etc. For online activities, group manager and local physicians will provide healthy lifestyle information and skills (e.g., exercise guidance, recipes) as well as self-management skills with the support of health tools (e.g., fitness aids such as elastic bands) in WeChat groups and one-on-one communication by WeChat or phone. Offline interventions will be guided by cognitive behavior therapy (CBT) [40] at local health centers through group managers, with group managers and physicians designing and recording related healthy lifestyle promotion activities. During the intervention, investigators will record participants' responses and satisfaction with the intervention and obtain their daily health records (e.g., photos of meal preparation following recommended recipes). For individuals with good adherence to the intervention or improved physical examination indicators, value-added gifts (e.g., household goods) will be released as rewards.

### Data collection and outcomes

Questionnaires and scales will be administered in onsite face to face interviews at baseline, 3, 6, 9, and 12 months. Face to face interviews will be conducted by trained research assistants (students). Physical examinations will be conducted by community doctors with at least 5 years of clinical experience. Biological samples such as blood and stool samples will be collected by trained nurses and delivered to specialized laboratories with procedures to keep the cooling chain and avoid contamination.

#### Primary outcomes

The primary outcome is the reduction of modifiable unhealthy lifestyles immediately after intervention (6 months). Unhealthy lifestyles considered comprise smoking, excess alcohol consumption, physical inactivity, unbalanced diet, and overweight/obesity (representing balance between energy intake and energy expenditure). Items as formulated in the Healthy Lifestyle Index Score (HLIS) from the European Prospective Investigation into Cancer and Nutrition cohort study [41], will be used to measure these lifestyles (see Table 2). Assessment of body mass index (BMI) and categorization into overweight/obesity will rely on relevant recommendations according to Chinese guidelines [42], while dietary index is based on the Mediterranean Diet Score [43]. For reasons of simplicity each lifestyle will be coded as a dichotomous variable with 0 indicating absence, 1 indicating presence of a particular unhealthy lifestyle. The decrease of unhealthy lifestyles by at least one at 6 months is considered favorable.

**Table 2 Tab2:** Components of lifestyle risk score

Components	Score	Measurement	Definitions in the study
Smoking status	0–4	Questionnaire • History of smoking in the past	Never = 4, ex-smokers quit > 10 years = 3, ex-smokers quit ≤ 10 years = 2, current ≤ 15 cigarettes/day = 1, current > 15 cigarettes/day = 0 [41]
Alcohol intake	0–4	Questionnaire • Alcoholic beverage consumption per day	low consumption of alcohol (< 6.0 g/day = 4, 6.0–11.9 g/day = 3, 12.0–23.9 g/day = 2, 24.0–59.9 g/day = 1, 60 + g/day = 0) [41, 44]
Physical activity	0–4	International Physical Activity Questionnaire • Number of hours per week spent in moderate to vigorous activities, vigorous-intensity PA	Metabolic equivalent tasks for four activity domains (occupational PA; transportation PA; PA for housework; sports and leisure-time PA): fifth quintile = 4, fourth quintile = 3, third quintile = 2, second quintile = 1, first quintile = 0 [41]
Dietary factors	0–4	Food Frequency Questionnaire • MDS, a linear score that incorporates 9 nutritional components of the Mediterranean diet [45]	Scoring 4 to 0 points for top to bottom quintile of the MDS: fifth quintile = 4, fourth quintile = 3, third quintile = 2, second quintile = 1, first quintile = 0 [44]
Overweight/obesity	0–4	Medical examination • BMI	< 22 = 4, 22–23.9 = 3, 24–25.9 = 2, 26–27.9 = 1, ≥ 28 = 0 [46]
Total score	0–20	Total of unweighted five components	

*BMI* Body Mass Index, *MDS* Mediterranean Diet Score, *PA* Physical activity

